#### Moderator and Mediator Analyses

Potential treatment effect moderators will be tested by including their main effect and interaction with the treatment group in multivariable regressions. For the analysis of potential mediators, we will employ the four-step logistical process of testing mediational effects developed by Baron and Kenny [63] and others and summarized by Frazier et al [64]. We will also use structural equation modeling techniques to examine the full pattern of predicted mediational pathways. We propose to develop a series of three models to examine how the proposed interventions influence the process of smoking behavior change. The first step in the process is to examine if there is any relationship between the proposed intervention and behavioral determinants as defined by our theoretical model. This step will involve the development of models, with each key behavioral determinant being the dependent variable (Model A). The next model will examine how changes in behavioral determinants are related to interim outcomes, that is, week 16 outcomes (Model B). The final model will examine how changes in behavioral determinants at the interim (16 weeks) evaluation are related to the outcomes at the final evaluation (26 weeks; Model C).

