### Participants

Prior to participant enrollment, all study procedures were approved by the Institutional Review Board. Participants called a designated study phone line to be screened for eligibility. All eligibility assessments were conducted over the phone, and initial eligibility status was determined immediately upon completion of the assessment.

A total of 195 participants were enrolled in this study (Figure 2). Recruitment occurred over 21 months, from June 2011 to March 2013. Final follow-up assessments were completed in August 2013. Participants were randomized to either biomarker feedback (active, n=98) or health education (control, n=97) conditions. Eligible participants were female. Although we initially allowed for enrollment of male parents/guardians, we discovered that our counselor did not feel comfortable conducting home visits with a male participant. Participants were at least 18 years of age, not planning to move out of the state over the next 3 months, willing to complete three assessments in their home over a 26-week study period, and the legal guardian of a child aged ≤10 years who lives in the home on at least 5 days of the week. In order to increase the likelihood that the home environment and the child’s urine assay would contain detectible tobacco toxins, participants were eligible if they endorsed smoking cigarettes on ≥20 days in the past 30 days, although they did not have to endorse smoking in the home. Participants were ineligible if they were pregnant, currently using any tobacco cessation aid (eg, counseling or NRT), homeless, living in a shelter or detox facility, living outside of a 30-mile radius of the university, or enrolled in a tobacco research study in the preceding 30-day period.

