#### Treatment Effect Moderators/Mediators

In order to examine psychological mediators and moderators of the proposed intervention (exploratory aims), key factors related to important determinants of smoking behavior change were selected for each set of analyses. These included proposed moderators of effect including sociodemographic variables for parent and child, baseline smoking, and social environmental variables. Participants were asked to detail the number of days they smoked in the last 30 days, the number of cigarettes they smoked on days they smoked, use of smokeless tobacco products and other tobacco used in the last 30 days, whether they used mentholated cigarettes, the number of 24-hour quit attempts they made in the past year, the longest time period they had without smoking a cigarette, and their lifetime nicotine replacement therapy use. Other tobacco-related variables included nicotine dependence, measured using “time to first cigarette” [49] and readiness to quit smoking [50]. Alcohol use [51] (ie, number of days one drank at least one drink, number of days one drank five or more drinks) was also assessed. Social environmental variables included the number of smokers living in the home, number of adult nonsmokers living in the home, outdoor smoking options, location where most smoking occurs, and adoption of home smoking restrictions in the home and car. Child exposure to tobacco smoke was also measured (ie, exposure to tobacco smoke in the home and outside the home in the past week). To assess any potential illnesses or health conditions that might impact the intervention or its effectiveness, parents were asked the following: “Has any health care provider ever told you that your child has any of the following illnesses: (eg, asthma, allergies, cancer, heart problems)?” Psychosocial variables included depressive symptoms (assessed using the 10-item Center for Epidemiological Studies Depression Scale [52]) and stress (measured using the 4-item Perceived Stress Scale [53]). Social influence was measured by asking how many of the participant’s five closest friends smoked cigarettes [54], and social support was measured via the Partner Interaction Questionnaire (Short-Form) [55]. Participants’ view of their social standing in the community and the nation was assessed using the MacArthur Scale of Subjective Social Status [56].

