#### Sample Size and Power Considerations

The sample size was chosen to ensure adequate power in order to examine the efficacy of tobacco-specific biomarker feedback in terms of the difference of SHS home exposure (primary outcome) between the two treatment groups at week 26. The power calculation was based on two-sided, two-sample *t* test assuming a type I error of 0.05. A total sample size of 180 (90 per treatment group) was determined to achieve 85% power in order to detect an expected difference (between 1.15 [SD 1.58] μg/m^3^ for the biomarker feedback group and 1.89 [SD 1.68] μg/m^3^ for the health education group) in air nicotine levels measured by dosimeters, which was derived from the assumed adoption rates of home smoking bans of the two treatment groups (55% vs 25%).

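### The four-step mediation process named for the exploratory aim loses much power when the total effect is small, and no indirect effect with an interval is made the test of mediation

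*Protocol article*

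**What the plan says.** Everything here is in the Protocol article.

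- **Status of the aim.** Treatment Effect Moderators/Mediators opens with "In order to examine psychological mediators and moderators of the proposed intervention (exploratory aims", so mediation is exploratory.
- **Named method.** Moderator and Mediator Analyses adopts the "four-step logistical process of testing mediational effects" attributed to Baron and Kenny and others, and points to a second source that summarizes it. The steps are not written out.
- **Second method.** The same section adds structural equation modeling of the mediational pathways. It does not say which quantity from that model is the test of mediation, or which method decides if the two disagree.
- **Three models.** Model A relates the intervention to the behavioral determinants. For Model B: "The next model will examine how changes in behavioral determinants are related to interim outcomes, that is, week 16 outcomes (Model B"). Model C relates determinants at week 16 to outcomes at week 26. None is made conditional on a significant treatment effect.
- **Size of the trial.** Sample Size and Power Considerations gives "A total sample size of 180 (90 per treatment group"), which "was determined to achieve 85% power" for the primary outcome. Participants gives "A total of 195 participants were enrolled in this study".

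**The concern.** The classical four steps are: arm affects outcome (total effect), arm affects mediator (path a), mediator affects outcome given arm (path b), and the direct effect of arm (c′) shrinks once the mediator is in the model. The first is a significance test on the total effect. The procedure declares mediation from the pattern of separate tests and gives no estimate or interval for the indirect effect a×b. Models A to C also take one link at a time.

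Two things follow. If the intervention's total effect is small, or a direct effect runs the other way, the first step can fail although both paths are well supported. And the four steps and the structural equation model can then give opposite answers on the same data, with no stated rule for which one counts.

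Model B adds a smaller problem of time order. Assessment visits were at baseline, week 16 and week 26, so most determinants in Model B and the outcomes they are related to were apparently measured at the same visit.

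**Working it through.** **1. The plan's own figure.** Inputs from Sample Size and Power Considerations: means 1.15 (SD 1.58) and 1.89 (SD 1.68) μg/m³, two-sided test, "assuming a type I error of 0.05", 90 per arm.

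- Pooled SD = √((1.58² + 1.68²)/2) = √2.6594 = 1.631. Difference = 1.89 − 1.15 = 0.74. d = 0.74/1.631 = 0.454.
- n per arm for 85% power = 2(1.960 + 1.036)²/0.454² ≈ 87.2, so 88. The stated 90 is reproduced.
- Power at 90 per arm = Φ(0.454 × √45 − 1.960) = Φ(1.084) = 86.1% (85.7% with the noncentral t).

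If the design effect is true, a total-effect step therefore passes about 86% of the time.

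**2. The mediation model.** The documents give no path sizes, so those below are assumptions. M = aX + e₁ and Y = c′X + bM + e₂, with unit residual SDs and arms one unit apart in X. The total effect in SD units is (ab + c′)/√(1 + b²).

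**3. A hand check at n = 195, with a = 0.5, b = 0.3, c′ = 0.**

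- Total effect = 0.15. Its SE = √1.09 × 2/√195 = 1.044 × 0.1432 = 0.1495, so z = 1.00 and power is about 17%.
- Path a: z = 0.5/0.1432 = 3.49, power 94%. Path b: z = 0.3 × √195 = 4.19, power 99%. Both together: 0.937 × 0.987 = 92%.

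Simulation of this case (3,000 trials) gave 16.3% for the four steps and 92.5% for a Monte Carlo interval on a×b. Nearly all the loss comes from the total-effect step.

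**4. Simulation at n = 180** (10,000 trials per row; the interval uses the first 3,000). Lenient means that the total effect, a and b are all significant. Strict also requires a non-significant direct effect.

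| a, b, c′ | Total d | Total step passes | Lenient | Strict | 95% interval on a×b |
|---|---|---|---|---|---|
| 0.4, 0.3, 0 | 0.12 | 11.4% | 9.8% | 8.0% | 73.1% |
| 0.5, 0.4, 0 | 0.19 | 23.5% | 22.9% | 21.0% | 91.3% |
| 0.5, 0.5, −0.25 | 0.00 | 4.8% | 3.9% | 2.3% | 92.2% |
| 0.4, 0.3, 0.3 | 0.40 | 75.9% | 59.4% | 22.9% | 73.5% |
| 0.8, 0.57, 0 | 0.40 | 74.7% | 74.7% | 72.4% | 99.9% |
| 0.5, 0.5, 0.27 | 0.47 | 87.7% | 82.0% | 44.3% | 91.4% |
| 0.6, 0.42, 0.26 | 0.47 | 88.2% | 87.0% | 49.4% | 98.4% |

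In the last two rows about half the effect is mediated: 0.25/0.52 = 48% and 0.252/0.512 = 49%. Also asking that the direct estimate be smaller than the total changes the lenient column noticeably only in the cancelled row (3.9% to 2.4%). At n = 195 every entry is equal or higher, by at most 5.7 points.

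**5. Error rate.** With one path set to zero at n = 195, the interval excluded zero in 5.1% and 4.9% of trials. The gain in power does not come from a loose test.

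**The case against.** The case on the other side is substantial.

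- **The mediation aim does not stop on a null primary result.** A reader might infer that it does. The article contains no such rule. The first step it spells out is arm to determinants (Model A), and Models B and C and the structural equation modeling carry no condition on the total effect. A total-effect requirement comes only with the classical four-step method. Whether the version in the two cited sources keeps that step, or adds an indirect-effect test, cannot be checked here. This objection stands.
- **The indirect effect is not ruled out of the plan.** A reader might infer that it is never tested. Structural equation modeling can estimate and test it. What remains is that the article does not make it the test, while it does name the four steps.
- **The four steps would not usually miss a mediator in this trial.** The 16% case in the hand check has a total effect of 0.15/1.044 = 0.14 SD, about a third of the design value of 0.45. With a total d of 0.40 to 0.47 and a lenient fourth step, detection is 75% to 87% for a strong mediator and 59% for a weaker one. This also stands.
- **Model C already has the right time order.** True. Model B needs only to be read as descriptive.
- **More intervals mean more false positives.** The article lists several mediators. Taking eight, each with one path truly zero and tests independent, the chance of at least one false finding is 1 − 0.95⁸ = 34%. The 5% error rate holds for one mediator at a time.
- **The detail may sit in a fuller plan.** That covers the interval method. It does not cover the choice of the four-step process, which the article makes in words.

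**Conclusion.** The point holds in limited form. The article names a mediation method that, in its classical form, loses much power when the total effect is small or cancelled: about 4% to 23% detection against 73% to 92% for an interval on a×b. Near the design effect with a strong mediator and a lenient fourth step, the loss is 9 to 25 percentage points (75% to 87% against 91% to over 99%). A strict fourth step brings detection in the two half-mediated cases down to 44% and 49%, and the article does not say which reading applies.

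These figures rest on assumed path sizes, one mediator, linear models, a continuous outcome and complete data. The documents do not support saying that the aim would be abandoned after a null primary result, or that the trial would usually miss a real mediator. The aim is exploratory, and neither the primary comparison nor the sample size is affected. It is still worth changing, because a better test is available from the same data.

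**What to change.** - For each mediator, make the indirect effect the test: the product of coefficients, or the same quantity from the planned structural equation model, with a 95% bootstrap interval. Report it whether or not the total effect is significant.
- Use the week-16 mediator adjusted for its baseline value, and the week-26 outcome adjusted for arm and baseline outcome. This is Model C's time order. Treat Model B as descriptive.
- For binary outcomes such as home smoking bans, state the scale on which the indirect effect is defined.
- Label the intervals exploratory, or adjust them for the number of mediators.

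The cost is a change of wording and a re-run on data already collected. The article reports that analyses are complete, so the indirect effects should be shown beside any four-step results and the change of method stated openly. The downside is a longer list of exploratory intervals, some of which will exclude zero by chance.

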## Results

Ethical approval was received from the University of Minnesota’s Human Research Protection program (Institutional Review Board code number: 0909M72004). Enrollment and analyses for the study are complete, and data interpretation is underway.

## Discussion

Project STARS is one of the first community-based trials to use culturally sensitive biomarker feedback given to the smoking parent or caregiver on their child’s exposure to tobacco toxins. The goal of the study was to reduce SHS exposure in the home, and the intervention was designed to target the smoking mother or female guardian of the child. However, there could be multiple smokers in the home (ie, spouse, partner, or grandparent). Participants were counseled on how to discuss SHS and negotiate home smoking restrictions with others living in the home or visiting the home, but family and social dynamics often complicated the execution of the rules. Further, the majority of our participants lived in areas of high social and economic disadvantage and had competing priorities and additional stressors in their lives that made smoking restrictions difficult. Their desire to create a smoke-free environment for their children was hindered by their physical environment and their responsibilities to care for their children. For example, it was not always plausible to smoke outside of their apartment because the neighborhood was not safe or they could not leave their child alone in the building without supervision. A series of focus groups with smoking mothers in disadvantaged areas found that the need to protect their child’s health was clearly set against competing demands, such as the need to relax and maintain social relationships and the need to be actively present to care for the child and prevent them from harming themselves [65].

Another potential complication was the amount of time the child spent outside of the home. To be considered eligible, the child had to be present in the home 5 days a week, but the number of hours spent in the home was not specified. The child may have spent time in other homes where smoking occurred. Further, children may have ridden in cars, other than their mother’s car, where a driver or passenger was smoking. Although this was assessed in follow-up surveys, it is difficult to obtain an accurate picture of the amount of time the child spent with other smokers. This will be important to keep in mind as we analyze the data from the nicotine badge and the child’s urine assays, as the two sources of measurements may not correlate with each other.

## Appendix

Multimedia Appendix 1 Peer-reviewer report from the National Center on Minority Health and Health Disparities.

## Abbreviations

CBPR: Community-Based Participatory Research
MAPS: Motivation and Problem Solving
REDCap: Research Electronic Data Capture
SHS: secondhand smoke
STARS: Start Taking Action to Restrict Smoking
THS: thirdhand smoke
